### Methodology of additional examinations and tests

#### Device control

Device interrogation is performed on every control visit. It should include: a standard battery and lead control, analysis of the histograms, alerts (especially arrhythmic), history of the ‘mode switch’ episodes (in order to evaluate AF burden) and BiVp% (measured from the last control visit). In case of CRT-D devices, the episodes of arrhythmia as well as the number of adequate and inadequate high-voltage intervention should be registered. If required, necessary modifications in the identification and treatment of ventricular arrhythmias should be made.

Moreover, during the visit a review of pharmacological treatment is performed, including analysis of its efficacy, validity, and occurrence of adverse effects. If required, necessary modifications in the pharmacological treatment, an eventual decision to change the *rhythm control* for the *rate control* or a decision to perform AVJA should be made. If an intervention of a device occurs, the additional device control should be performed.

#### Echocardiography

Participants will undergo an echo test (Philips Matrix iE33, Philips Ultrasound, Bothell, WA, USA) performed with a general assessment of morphology and function of the heart.

Echocardiography will include the evaluation of:

Cardiac dimensions (including diameter, area and volume of left atrium)Left ventricular global systolic function (EF% and volumes, dp/dt), left ventricular regional function (extent and localization of infarct scar) and left ventricle diastolic functionType of diastolic dysfunction, diastolic pressure in the left ventriclePresence and severity of valvular diseases (particularly mitral regurgitation)Evaluation of cardiac dyssynchronyIntraventricular dyssynchrony parameters ('septal flash' and septal to posterior wall motion delay, septal to lateral time to peak systolic point from R-wave on electrocardiogram (Ts) delay)Atrioventricular dyssynchrony: diastolic filling ratio (LVFT/RR)Interventricular dyssynchrony (difference between left ventricular and right ventricular pre-ejection time in pulsed-wave Doppler and/or a delay between the onset of systolic motion in the basal right ventricular free wall versus the most delayed basal LV segment in tissue Doppler)

In patients with sinus rhythm, an AV interval will be optimized (unless optimization had been performed previously).

#### Cardiopulmonary exercise test

CPXs on a treadmill (Marquette T2000, GE Healthcare, Little Chalfont, UK) with standardized modified Bruce or Naughton exercise protocols will be applied. Breath-to-breath respiratory gas analysis will be carried out with Vmax Encore 29c equipment (Viasys Healthcare, San Diego, CA, USA). An exercise test will be carried out until maximal patient’s exertion, maximal heart rate or dangerous ventricular arrhythmia occurs. The following parameters will be monitored during CPX:

Heart rate, arterial blood pressure, ST segment changesPeak oxygen uptake (peak VO_2_, ml/kg/minute, l/minute)Peak VO_2_ as percentage of normalized VO_2_ in given populationPeak carbon dioxide exhalation (peak VCO_2,_ l/minute)Oxygen pulse (O_2_ pulse, ml/heart rate)Maximal minute ventilation (VE, l/minute)Breathing reserve (BR): maximal voluntary ventilation/maximal exertional ventilation × 100%Heart rate reserve (HRR): maximal HR/peak exertional HR × 100%Anaerobic threshold level (ml/kg/minute)Maximal CO_2_ equivalent: VE/VCO_2_ maxVE/VCO_2_ slope and VE/VO_2_ slopeSubjective dyspnea level (according to Borg scale from 1 to 5, where 5 is maximal dyspnea)

Exertional level will be assessed subjectively by patients in Borg scale (6 to 20, where 6 means no exertion, 20 - maximal exertion).

## Statistical methods

### Sample size

The calculation of a sample size was made based on the estimated results in the groups for the primary endpoint (BiVp%) and the following assumptions: 1) the mean difference of BiVp% between groups would be 8% and standard deviation (SD): 15%; 2) probability of a type I error: 0.05; 3) probability of a type II error: 20%; 4) the type of test: Student’s two-sample *t*-test; 5) drop-out rate: 8%.

A power analysis revealed that a minimum of 30 patients per group will be required to assure at least 80% power for detecting the anticipated between-group differences in BiVp% and to compensate for the expected drop-out rate.

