### Statistical analysis

Baseline demographic characteristic and clinical variables will be summarized for each arm of the study. Continuous data will be presented as arithmetic means and SD for normally distributed variables or as medians and inter-quartile ranges (25 to 75th) for abnormally distributed variables. Normality will be tested by the Shapiro-Wilk test.

Comparison of two groups will be based on parametric Student’s two-sample *t*-test, or Cochran-Cox test or non-parametric Mann–Whitney test as appropriate. Student’s paired *t*- or Wilcoxon’s test will be used to compare continuous variable differences between baseline and the end of observation period.

Categorical data will be given as absolute and relative frequencies (percentages). The differences in proportions between them will be examined using the chi-square - test with Yates’s correction or Fisher’s exact test as appropriate.

A logistic regression model will be used to identify independent predictors of response to therapy. For the longitudinal analysis, curves of cumulative probability of events will be constructed according to the Kaplan-Meier method, and the cumulative events rates will be compared by the log-rank test. A Cox proportional hazards regression analysis will be performed to assess for any potential influence of covariates. The assumptions of the Cox proportional hazards model will be checked by visual inspection of the log-log survival function by time curve.

Due to the possibility of the treatment crossovers, all major treatment comparisons between the randomized group in this trial will be performed according to both the intention-to-treat and the per protocol principles.

All null hypothesis will be two-tailed with a 0.05 type I error rate.

Statistical analysis will be performed using the SAS 9.2 statistical package (SAS Institute Inc., Cary, NC, USA).

The investigation conforms with the principles outlined in the Declaration of Helsinki [21]. The local ethics committee (that is the Ethics Committee of the Institute of Cardiology, Warsaw, Poland) has approved the study protocol including the written informed consent form (approval number: IK-NP-0021-47/1378/13).

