## Discussion

Based on the current knowledge, the authors assume that the *rhythm control* strategy would be at least as good as the *rate control* strategy in terms of BiVp%. The achievement of SR and satisfactory BiVp% in the *rhythm control* group may strengthen the underestimated position of cardioversion in the group of HF patients on CRT with concomitant permanent AF.

It may seem disputable whether the CRT patients with permanent AF will resume and maintain SR. As has been already mentioned, HF and AF are diseases that can negatively influence each other. In at least some of the patients, an occurrence of AF seems to be a marker of HF severity. We hypothesize that restoration of sinus rhythm, which would enhance the performance of CRT and enable better treatment of HF, may have beneficial effect on AF progression. Based on the evidence of the SR resumption phenomenon [13] and the study by Turco *et al*., this is highly probable. In the latter work it has been proven that - by means of a single cardioversion - SR is resumed in 82% of the patients and maintained for a 1 year in about 60% of the former AF-CRT patients [14]. We assume that the possibility of additional cardioversions and standard use of the amiodarone will elevate this percentage. Additionally, the results of the PVI isolation from the PABA-CHF trial in HF patients with AF are also appealing bearing in mind the initial differences between the populations of the PABA-CHF and our study (that is the lack of CRT in the PVI subgroup and paroxysmal character of the AF in half of the patients). After a 6-month observation period, 88% and 71% of patients who underwent PVI were free from AF depending on whether they received or did not receive antiarrhythmic agents [18].

The authors are fully aware that during the progression of HF, irreversible fibrous changes within the atria occur which promote AF and its maintenance [22], so it is unlikely that the proposed treatment strategy would be effective in all of the patients included. Hence, it seems crucial not only to establish the efficacy of proposed treatment strategy of rhythm control but also to define the subgroup of patients who would benefit the most from this strategy. An attempt to perform preliminary analysis of the non-responders as well as the ultra-responders would be made in the trial.

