The standard use of amiodarone in both of the groups may seem disputable in the potential complications of this treatment and limited evidence of its efficacy. However, following the literature the use of amiodarone should facilitate sinus rhythm maintenance in the rhythm control group [1, 23, 24]. The use of the drug in the *rate control* group arises from its beneficial effect on AV node in this group of patients [1]. Moreover, it makes two of the treating arms more consistent. Following the latest ESC guidelines on management of AF [1], amiodarone is commonly used in patients with AF and depressed left ventricle ejection fraction and its potential adverse events, occurring in up to about 10% of patients according to the latest RCT comparing amiodarone with dronedarone [24], will be carefully monitored, including regular TSH measurements, QT evaluation and occurrence of arrhythmias at baseline visits and during the follow-up period.

One of the limitations of the trial is the number of the participants which surely has an impact on the statistical strength of the study. It would enable the researchers to assess the efficacy of the two treatment strategies on the primary endpoint only. The statistical difference within the clinical secondary endpoints of this study will be difficult to achieve. However, the lack of sufficient data about the CRT in the patients with concomitant AF necessitates the undertaking of an initial pilot study upon this issue.

The incoming results of the Pilot-CRAfT would enable the authors to prepare a parallel larger, well-designed multi-center study assessing the influence of both treatment strategies on ‘harder’ clinical endpoints, such as mortality and morbidity, as well as further analysis of the factors determining the response to the rhythm control strategy. The assessment of the efficacy of the rhythm control strategy in CRT and AF patients and the identification of the subgroup of patients who benefit from it the most would create an alternative to the currently recommended rate control strategy which has some considerable limitations.

Whatever the results of the trial, performing a prospective, randomized study on CRT patients with concomitant persistent forms of AF would finally provide strong scientific evidence data about the efficacy of CRT in this specific subgroup of patients. This urgently needed data has been long awaited.

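### On the protocol's own sample-size inputs, 30 patients per group give about 50% power for the primary endpoint, not the stated 80%

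*Protocol article*

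**What the plan says.** The protocol article, under Sample size, assumes that "the mean difference of BiVp% between groups would be 8% and standard deviation (SD): 15" per cent. It adds "probability of a type I error: 0.05", "probability of a type II error: 20" per cent, "4) the type of test: Student’s two-sample" t-test, and 8% drop-out. From these it concludes that "a minimum of 30 patients per group will be required to assure at least 80% power" and that the same number also absorbs the drop-out.

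Sidedness is set under Statistical analysis: "All null hypothesis will be two-tailed with a 0.05 type I error rate". Allocation is 1:1 (Principles of the management of the patients) and the trial enrols 60 patients (Study scheme).

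The Discussion lists the number of participants as a limitation that affects statistical strength. It then says of the trial's size: "It would enable the researchers to assess the efficacy of the two treatment strategies on the primary endpoint only". The primary endpoint is therefore presented as the one question the trial is large enough to address.

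**The concern.** A standardised difference of 8/15, or 0.53, is a moderate effect. A two-sided two-sample comparison at 80% power needs more than 50 patients per group for an effect of that size, so 30 per group with drop-out included cannot be right.

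The figure concerns the primary endpoint, and the article prints both the inputs and the output. The mismatch is therefore internal to the section and is not a detail left to another document. If the true power is near 50%, the trial is about as likely to miss the effect it was sized for as to find it. Readers who trust the 80% would give a non-significant result more weight than it can bear.

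**Working it through.** **Inputs.** Difference 8 points, SD 15 points (read as the per-group SD), alpha 0.05, type II error 20%, two-sample t-test and 8% drop-out, all from Sample size. Two-sided testing is from Statistical analysis. Allocation is 1:1.

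**Can the stated 30 be reproduced?**

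- *Two-sample formula, normal approximation:* n per group = 2 × [SD × (1.960 + 0.842) / difference]² = 2 × (15 × 2.802 / 8)² = 55.2, so 56. This does not give 30.
- *Same formula without the factor 2:* (15 × 2.802 / 8)² = 27.59, and 27.59 / 0.92 = 29.99, so 30.
- *Per-group figure taken as the total:* 55.2 / 0.92 = 59.99, so 60 in total.
- *Exact one-sample t-test:* 29.6, so 30 before any drop-out allowance.

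Several routes lead to the printed number. None of them is a two-sample calculation that yields 30 per group on the stated inputs.

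**Required size, exact (noncentral t, effect 8/15).** 56.2, so 57 evaluable per group, with power 80.6% at 57. With drop-out, 57 / 0.92 = 61.96, so 62 per group or 124 in total, about double the planned 60.

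**Power at the planned size.** The noncentrality parameter is (8/15) × √(n/2), with 2n − 2 degrees of freedom. Drop-out leaves 30 × 0.92 = 27.6 per group, taken as 28.

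| Analysed per group | Noncentrality | Power, exact t | Power, normal approx. |
|---|---|---|---|
| 30 | 2.07 | 52.8% | 54.2% |
| 28 | 2.00 | 50.0% | 51.4% |
| 27 | 1.96 | 48.5% | 50.0% |

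**What the planned size can detect at 80% power.** With 28 per group the standardised effect is 0.762, so the difference is 0.762 × 15 = 11.4 points; for a difference of 8 the SD would have to be 8 / 0.762 = 10.5. With 30 per group the effect is 0.736, giving a difference of 11.0 points or an SD of 10.9.

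**Precision.** The half-width of the 95% confidence interval at 28 per group is 2.005 × 15 × √(2/28) = 8.04 points, about the size of the whole target effect.

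**Readings that might rescue the figure.**

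- *One-sided 0.05.* This contradicts the Statistical analysis section. It still needs 45 per group before drop-out (exact 44.2) and gives 65.4% power at 30.
- *15 as the SD of a difference.* The per-group SD would be 15 / √2 = 10.6. Power is then 81.9% at 30 and 79.2% at 28, so the claim would nearly hold.
- *Baseline adjustment.* The required sample shrinks by 1 − r². Getting from 57 to 28 or 30 needs r = √(1 − 28/57) = 0.71 or √(1 − 30/57) = 0.69. The article states no such correlation, and its group comparisons are unadjusted tests.

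**The case against.** The strongest defence concerns the SD. The article gives 15% directly beside the mean difference and does not say whose SD it is. If it was meant as the SD of a difference, the arithmetic is almost right and the fault is an undefined input. This cannot be excluded from the text. However, next to a named two-sample t-test the ordinary reading is a per-group SD, so the authors need to clarify the term before the 80% can stand.

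A second defence is that this is a pilot whose authors admit its limited size. That is true, but the Sample size section still makes a definite 80% claim, and the Discussion exempts the primary endpoint from the limitation.

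A reader might also infer more than the documents support:

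- *That the factor of 2 is known to have been dropped.* The match at 29.99 is striking, but no formula is printed and other routes reach the same number.
- *That a null result will be presented as showing equivalence.* The Discussion does assume that rhythm control "would be at least as good as the" rate-control strategy. That is an expectation. The plan is a test of difference, and nothing says how a non-significant result will be read.
- *That the later, larger trial will carry the error forward.* The article says that trial will address mortality and morbidity using data from this one. It does not say this calculation will be reused.

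**Conclusion.** The power statement is wrong as written. On the stated inputs, 30 per group gives between 50.0% (28 analysed) and 52.8% (all 30 analysed), against a claim of at least 80% with drop-out included. The claim would need 62 randomised per group. This is a shortfall of roughly 30 percentage points on the primary endpoint, and it should be corrected.

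The conclusion rests on 15 being the per-group SD, on two-sided testing as the article states, and on an unadjusted two-sample comparison. It does not depend on how the error arose. Only a different meaning of the SD would largely restore the figure, to about 79% after drop-out, and the article does not state that meaning.

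**What to change.** Keep N = 60 and correct the text.

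1. In Sample size, replace the power sentence with wording such as: *30 patients per group (28 evaluable after 8% drop-out) give about 50% power for a difference of 8 points with SD 15, and 80% power for a difference of about 11.4 points; 80% power for 8 points would need 57 evaluable (62 randomised) per group.*
2. State what the SD of 15 refers to. If it was the SD of a difference, say so, give the per-group SD of about 10.6, and state the resulting power of about 79% at 28 per group.
3. Amend the Discussion sentence on the primary endpoint so that it no longer implies adequate power there.
4. Report the primary result as the estimated difference with its 95% confidence interval (half-width about 8 points at 28 per group), so that a non-significant test is not taken as evidence of no difference.

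The cost is a few sentences and a less favourable stated power. No extra patients are required. Enlarging the trial to reach 80% for 8 points would be a separate choice for the sponsor.

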### Randomization

Randomization will be provided by independent statistician using SAS 9.2 software (SAS Institute Inc., Cary, NC, USA). Permuted block randomization will be used (blocks AB and BA). Once an eligible patient gives his informed consent, he will be given a specific, unique identifier. The statistician will monitor the enrollment process.

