### Study scheme

The Pilot-CRAfT study is a single-center, open, prospective, randomized controlled trial. The trial enrolls 60 patients with HF and concomitant permanent or long-standing persistent AF who underwent CRT implantation at least three months before the enrollment in the Second Department of Coronary Artery Disease of the Institute of Cardiology in Warsaw, Poland. The inclusion and exclusion criteria are listed in the Table 1. Before the enrollment each participant will give written, informed consent.

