### Principles of the management of the patients (treatment strategies)

The enrolled patients are randomly assigned to one of the two groups (in a 1:1 ratio). In the first group, a strategy to restore and maintain SR is implemented (that is rhythm control strategy - the active treatment group). In the second group, a strategy to slow ventricular rate will be implemented (that is rate control strategy - the control group).

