## Trial status

Ongoing - currently recruiting.

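### Published blocks of two in an open, single-centre trial let site staff who know the scheme foresee up to half of the allocations

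*Protocol article*

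**What the plan says.** The protocol article gives the allocation rule in its Randomization section: "Permuted block randomization will be used (blocks AB and BA". The same section assigns the task to someone outside the treating team ("Randomization will be provided by independent statistician using SAS 9.2 software") and describes registration: "Once an eligible patient gives his informed consent, he will be given a specific, unique identifier". It does not say when the assignment is released relative to these steps.

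Three other sections bear on the point:

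- Study scheme: "The Pilot-CRAfT study is a single-center, open, prospective, randomized controlled trial", with the size given as "The trial enrolls 60 patients with HF and concomitant permanent or long-standing persistent AF".
- Principles of the management of the patients: allocation to two arms in a 1:1 ratio.
- Trial status: "Ongoing - currently recruiting".

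The article mentions no stratification, no varying block size and no masking of the block size.

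**The concern.** A block of two holds one patient per arm. Once the first patient of a pair has been assigned, the second assignment is settled. In an open trial at one centre, the people who recruit can see that first assignment, and the block structure was there to be read in the article while patients were still being enrolled.

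Knowing the next arm matters only if enrolment leaves room for choice, and here it does. Exclusions such as significant valve disease or reversible causes of AF need judgement. Candidates must have had their device for at least three months, so the moment of approach is flexible. A recruiter who expects a patient to hold sinus rhythm, for instance because of a smaller left atrium, could bring that patient forward or hold the patient back according to the arm that comes next, even without intending to.

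The primary endpoint is the mean BiVp% over follow-up, and the Statistical analysis section describes two-sample comparisons between the groups. A difference in prognosis at entry would pass into that comparison as if it were a treatment effect. Reading BiVp% from the device limits biased assessment but does nothing about who enters which arm.

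**Working it through.** The article gives no figure for predictability, so there is none to reproduce. The inputs are block size 2 (Randomization), 60 patients (Study scheme), and the planning values in Sample size: "the mean difference of BiVp% between groups would be 8% and standard deviation (SD): 15" (both in percentage points).

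**1. Allocations fixed by the preceding one.** 60 / 2 = 30 pairs. One allocation per pair is determined, so 30 of 60, or 50%.

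**2. Correct guesses when always naming the arm that is behind.** First slot: probability 1/2. Second slot: probability 1. The average is (0.5 + 1) / 2 = 0.75, or 45 of 60. Simple randomization gives 0.50, or 30 of 60.

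**3. Would a larger fixed block be enough?** For a known block of four, the chances of a correct guess by position are 1/2, 2/3, 2/3 and 1. Their sum is 2.833, and 2.833 / 4 = 70.8%. Full enumeration gives:

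| Known fixed block size | Allocations determined | Correct guesses |
|---|---|---|
| 2 | 50% (30 of 60) | 75.0% |
| 4 | 33.3% (20 of 60) | 70.8% |
| 6 | 25% (15 of 60) | 68.3% |
| Simple randomization | 0% | 50% |

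A larger block that is still known helps only in part. Most of the gain has to come from varying the size and not disclosing it.

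**4. Possible bias.** On average half of each arm sits in second slots. Let *d* be the difference in prognosis between arms among second-slot patients, with none among first-slot patients. Then

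bias = ½ × 0 + ½ × *d* = *d* / 2.

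The documents give no value for *d*, so a range is assumed:

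| Assumed *d* (BiVp% points) | Bias | Share of the planned 8 points |
|---|---|---|
| 2 | 1 | 1 / 8 = 12.5% |
| 5 | 2.5 | 2.5 / 8 = 31% |
| 10 | 5 | 5 / 8 = 62.5% |

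**5. What a first-slot analysis would cost.** With SD 15 and 30 per arm, the standard error of the difference is 15 × √(2/30) = 3.9 points. With only first-slot patients, about 15 per arm, it is 15 × √(2/15) = 5.5 points. The check is free of this bias but imprecise.

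**The case against.** The best defence is that the list is held by an independent statistician, that patients are registered after consent, that the endpoint is read from a device, and that this is a pilot. The last three are fair context but leave the mechanism untouched. The first protects only the first slot of each pair: the second can be inferred without seeing the list.

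Stronger conclusions are tempting, but the documents do not support them.

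- *Concealment has failed throughout.* Only second slots are exposed, and only to someone who knows the block size and has followed the last assignment. One open site and a published scheme make that plausible; the article does not show that it happened.
- *Selection bias has occurred.* Nothing in the article shows it.
- *No procedure could protect blocks of two.* Randomizing both members of a pair together, after both have consented, would do so. The article does not describe this.
- *The analysis can do nothing.* Baseline BiVp% and echocardiographic measures are collected, so measured imbalance can be adjusted for, and first-slot patients can be analysed alone. Unmeasured differences remain, and the restriction costs about half the sample.

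The scope for steering also has limits: patients with a left atrium above 6 cm or a BiVp% of 95% or more are not eligible. A condensed article may also omit strata. If there are any, the same argument holds within each stratum.

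**Conclusion.** The point stands as a weakness in a rule that the article states, not as a missing detail. Up to 30 of 60 allocations can be foreseen, and a guesser is right 75% of the time instead of 50%. This rests on two assumptions: that recruiting staff know the block size and that they know the previous assignment.

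The effect on the result is a risk and not a finding. It is *d* / 2, or 1 to 5 BiVp% points for an assumed *d* of 2 to 10, against a planned difference of 8. The number of patients still to be enrolled is not given, so the share of allocations that can still be protected is unknown. The change is cheap while recruitment lasts; afterwards only the partial analytic checks remain.

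**What to change.** **Remaining patients.** Starting after a completed pair, the independent statistician generates a new list with randomly varying block sizes, for example 4 and 6. The sizes are not disclosed to investigators and not published before recruitment ends. Each assignment is released only after eligibility and consent have been irrevocably recorded.

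**Patients already enrolled.** Compare baseline characteristics by arm separately within first and second positions; arm differences confined to second positions would point to steering. Repeat the primary analysis in first-position patients, labelled as a low-powered sensitivity check.

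**Cost.** A new list and a protocol amendment, which will probably need to go back to the ethics committee that approved the protocol. The final imbalance could reach about 3 patients, if a last block of six is cut off after three assignments to the same arm. Switching in the middle of a pair could add one more (3 + 1 = 4), hence the start after a completed pair.
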